### Primary outcome data collection

Data collected from participants’ completed questionnaires forms the basis of the primary outcome. Questionnaires will be posted directly to the participant by the local site with a self-addressed envelope to enable the return of the questionnaires directly to the TOPIC 2 Trial Office. Participants will be asked to indicate their ‘worst chest pain over the last week’ on a visual analogue scale (VAS; 0–100). Presence of CPTP will be taken to be a score greater than or equal to 40 (mm) indicating at least a moderate level of pain.

### Plans to promote participant retention and complete follow-up {18b}

Throughout the recruitment and follow-up period, retention will be constantly assessed by the trial management group including patient representatives. A key strategy implemented to improve follow-up will be the provision of a thank you card and trial branded pen with the 6-month questionnaire to encourage completion of the questionnaire booklet which informs the primary outcome.

### Data management {19}

A secure database containing trial-related data will be maintained at the University of Birmingham. All research data will be stored on secure SQL servers at the University of Birmingham, to which only authorised users will have access. The University’s Data Protection Policy and the Conditions of Use of Computing and Network Facilities set out the security arrangements under which sensitive data should be processed and stored. All studies at the University of Birmingham are registered with the Data Protection Officer and data held in accordance with the General Data Protection Regulation. Data will be stored for a minimum of 10 years but with an expectation for storage up to 25 years.

### Confidentiality {27}

Personal data recorded on all documents will be regarded as strictly confidential and handled and stored in accordance with the General Data Protection Regulation and Data Protection Act 2018. In correspondence between the Birmingham Clinical Trials Unit and site staff, participants will only be identified using their unique trial identification number, date of birth and initials on the case report form. Participants will be asked to provide explicit consent for the transfer of a copy of their consent form (containing identifiable patient data) from the host site to Birmingham Clinical Trials Unit. This will be used to perform in-house monitoring of the consent process.

### Plans for collection, laboratory evaluation and storage of biological specimens for genetic or molecular analysis in this trial/future use {33}

Not applicable, no biological samples collected.

## Statistical methods

### Statistical methods for primary and secondary outcomes {20a}

The primary comparison groups will be those treated with PVB post operation versus those treated with TEB. All analyses will be based on the intention to treat principle, i.e. all participants will be analysed in the treatment group to which they were randomised irrespective of compliance or other protocol deviation but excluding patients that did not go on to have surgery. For all outcome measures, appropriate summary statistics will be presented by group (e.g. mean differences and relative risk) with supporting 95% confidence intervals. Intervention effects will be adjusted for the minimisation variables listed in Sect. 16a where possible. No adjustment for multiple comparisons will be made. A two-sided *p*-value of < 0.05 will be considered statistically significant. Statistical analysis will be performed using Stata version 17.

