#### Intervention group: PVB

Participating institutions ‘usual practice’ of PVB; three single-shot injections, at appropriate spinal levels supplying the skin over the incision site, will be given before the start of surgery. A PVB catheter will then subsequently be placed under direct vision during surgery. A loading dose is given before chest closure followed by continuous paravertebral infusion for post-operative use.

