#### Standard group: TEB

Participating institutions ‘usual practice’ of TEB; epidural catheter is inserted at the spinal level supplying the skin at the incision site, followed by test dose and a loading dose before the start of surgery. An epidural infusion is set up for use during the operation and for postoperative use.

In this intentionally pragmatic trial, some variation in technical aspects of block insertion is anticipated, both between experienced thoracic anaesthetists and surgeons, and between centres, as clinicians will use their judgement on the best insertion techniques for each individual patient. These include the following: insertion using ultrasound or landmark techniques, use of bupivacaine, levobupivacaine or ropivacaine and addition of opiate. This represents real-world variation in clinical practice and will not contribute to bias since randomisation will ensure balance across groups by centre. These variations in practice will be captured in the case report form.

Trial treatment and interventions (TEB or PVB) will be performed by thoracic anaesthetists or surgeons (consultants or senior trainees) with experience in the techniques, who have reviewed trial training material and confirmed that they are able to perform the techniques.

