#### Secondary outcomes

Complications of regional analgesia (failure of blockade, hypotension (systolic blood pressure (< 90 mmHg), inadequate pain relief, low respiratory rate (< 10/min), drowsiness, nausea and vomiting, urinary retention, itching, high block, post-dural puncture headache, vascular puncture, pleural puncture) until discharge from hospitalOccurrence and severity of surgical complications until discharge from hospital; occurrence as defined by the European Society of Thoracic Surgeons dataset [24] and severity as defined by the Thoracic Morbidity and Mortality (TMM) classification [25]Post-operative pulmonary complications (PPCs) until discharge from hospital (as defined by the standardised endpoints in perioperative medicine: pulmonary complications [26]Critical care admission (levels 2 and 3)Mortality (reported for all deaths due to all causes)Analgesic useAcute pain in the 3 days following surgery (patient reported via VAS; Brief Pain Inventory [27]; (Table 1))Pain at hospital discharge (via VAS, BPI and Short-form McGill Pain Questionnaire 2 (SF-MPQ-2 [28] (Table 1))Chronic pain (via VAS, BPI and SF-MPQ-2, completed by the participant at 3, 6 and 12 months post randomisation (Table 1))Resource use and cost data (resource use intraoperatively, during and following hospital admission, completed by the research team at each site and via telephone interviews with the patient following discharge, as appropriate)General health-related quality of life (by EQ-5D-5L [29], completed by the participant at hospital discharge and at 3, 6 and 12 months (Table 1))Mental health state (measured by Hospital Anxiety and Depression Scale (HADS [30]), completed by the participant at hospital discharge and at 3, 6 and 12 months)Serious adverse events

**Table 1 Tab1:** Data collection tools and corresponding outcomes

Collection tool	Outcome	Possible responses
Visual analogue scale (VAS)	Chronic phase: • Worst chest pain over the last week score (primary outcome) • Average chest pain over the last week score Acute phase: • Worst chest pain over the last 24 h score • Average chest pain over the last 24 h score	All 0–100 (higher = worse score)
Brief Pain Inventory questionnaire (BPI) [27]	Interference score	0–10 (higher = worse score)

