#### Secondary outcome assessment

Analysis on the presence of CPTP will also be performed at 3 months and 12 months, whilst all remaining secondary outcomes will be analysed at each time point, as appropriate. The presence of CPTP and mortality will be analysed similarly to the primary outcome. Questionnaire responses (VAS, BPI, EQ-5D, HADS and SF-MPQ-2) will be converted to scores and analysed using a mixed linear regression model, adjusting for the intervention group, baseline score (if available) and the minimisation variables (again, centre will be included as a random effects variable). Further supportive analyses will be carried out on questionnaire responses using a repeated measures [31] (multi-level) model incorporating all recorded scores (baseline and the three post-treatment scores). Parameters allowing for participant, intervention group, time, baseline score and the minimisation variables will be included. A random intercept component will also be included. Regarding safety, the total number of patients experiencing SAEs will be reported by intervention group along with a descriptive table of the events, and statistical significance will be determined by a chi-square test.

A separate statistical analysis plan has been produced and provides a more comprehensive description of the planned statistical analyses.

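### The no-surgery exclusion applies to every analysis, so a block event that stops the operation drops out of the between-arm safety comparison

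*Protocol article*

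**What the plan says.** Under Statistical methods for primary and secondary outcomes {20a}, the rule opens with "All analyses will be based on the intention to treat principle". It then explains that participants are kept in their randomised group "irrespective of compliance or other protocol deviation but excluding patients that did not go on to have surgery". The following sentence goes on to all outcome measures. The article names no separate safety population.

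The timing of the blocks is given under Interventions:

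- **TEB:** the epidural catheter is inserted, "followed by test dose and a loading dose before the start of surgery".
- **PVB:** three single-shot injections "will be given before the start of surgery". The catheter comes later: "A PVB catheter will then subsequently be placed under direct vision during surgery". Its loading dose is given before the chest is closed.

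The Secondary outcomes section counts complications of regional analgesia up to hospital discharge, among them hypotension and "high block, post-dural puncture headache, vascular puncture, pleural puncture". The participant timeline (Table 2) collects these complications, SAEs and deaths from day 0. Under Secondary outcome assessment, "the total number of patients experiencing SAEs will be reported by intervention group", with a chi-square test. Mortality is analysed in the same way as the primary outcome.

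**The concern.** Leaving out people who were never operated on is reasonable for chronic post-thoracotomy pain, which presupposes a thoracotomy. It is not reasonable for harms of the block, because exposure to the block starts before the operation. If a high block, a vascular puncture or severe hypotension leads the team to abandon surgery, the participant is removed because of the very outcome being compared.

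Three features make this more than a formality:

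- The exclusion happens after randomisation, which takes place on the day of surgery or the working day before.
- The clinicians who decide whether to proceed know the allocation.
- Exposure before incision differs between arms. The whole epidural insertion and loading comes first, whereas the paravertebral catheter and its loading dose come during the operation.

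Any bias would favour the technique with more operation-stopping events. Comparing complications is a stated secondary objective.

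**Working it through.** **Which participants the rule removes.** The points below come from Statistical methods {20a}, the two intervention descriptions, Table 2 and the adverse event section.

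| Participant | Exposed to a block? | Event recorded? | In the final between-arm comparison under {20a}? |
|---|---|---|---|
| Cancelled before any block | No | SAEs and deaths, yes | No |
| Block given, then operation abandoned | Yes | Yes, from day 0 | No |
| Block given, operation done | Yes | Yes | Yes |

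The second row is the problem. For block complications the first row is harmless, because nobody in it can have one. Among the listed complications, those that can arise at insertion or loading (vascular puncture, pleural puncture, high block, hypotension) are most exposed. Itching, urinary retention, inadequate pain relief and post-dural puncture headache would mostly appear after surgery and are barely touched.

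**The plan's own figure.** The sample size is not in dispute and serves here only for the denominator. With 30% versus 20%, two-sided 0.05 and 90% power:

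n = [1.960 × √(2 × 0.25 × 0.75) + 1.282 × √(0.30 × 0.70 + 0.20 × 0.80)]² / 0.10² = 392 per arm, as stated.

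Inflating for 10% deaths and a further 15% loss gives 784 / (0.90 × 0.85) = 1024.8, against 1026 stated. Per arm, 1026 / 2 = 513.

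**Illustration for SAEs.** The article gives neither an SAE rate nor a no-surgery rate, so these counts are assumptions. Suppose 50 participants per arm have an SAE after going to surgery, and k further TEB participants have a block SAE that stops the operation, with none in the PVB arm. The test is the chi-square without continuity correction, z² = (difference)² / [p(1−p)(1/n₁ + 1/n₂)], where p is the pooled proportion.

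| k | Block attempted (n = 513 v 513) | p | Under {20a} | p |
|---|---|---|---|---|
| 3 | 53/513 v 50/513 (10.3% v 9.7%) | 0.76 | 50/510 v 50/513 (9.8% v 9.7%) | 0.98 |
| 10 | 60/513 v 50/513 (11.7% v 9.7%) | 0.31 | 50/503 v 50/513 (9.9% v 9.7%) | 0.92 |

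Worked line for k = 10, everyone with a block attempted: p = 110/1026 = 0.1072; variance = 0.1072 × 0.8928 × 2/513 = 0.000373; difference = 10/513 = 0.0195; z² = 1.02; p = 0.31.

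In both rows the observed excess almost entirely disappears: 0.6 points become 0.1, and 1.9 points become 0.2. In neither row does the significance conclusion change.

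**The case against.** The strongest reply is that nothing is lost. Block complications go on trial-specific forms, and other serious events go on SAE forms with causality judged at site and again centrally. The data monitoring committee sees a full SAE assessment at least yearly. This stands. A reader might infer that such events vanish and that the trial would record zero in both arms, but the documents do not support that. What is lost is the participant's place in the final between-arm comparison.

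Second, the SAE sentence is introduced separately from the general rule, and the SAP, which is not shown, may define a safety population. That is possible. But the article does not merely leave the population open. It states a rule for all analyses, and the SAE sentence does not waive it. If the SAP says otherwise, the two should be reconciled.

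Third, the exclusion has an ordinary purpose: randomisation may fall on the day before surgery, and operations are cancelled for many reasons before any block is placed. The section on modifying allocated interventions also lets another technique be used when the allocated one cannot be performed, so a difficult block need not end the operation. Both points stand and suggest that the affected group is small.

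A reader might also take "The primary comparison groups will be those treated with PVB post operation versus those treated with TEB" to mean an as-treated comparison. The next sentence, and the separate statement that crossovers stay in their allocated group, settle the matter in favour of randomised groups. Only the wording is loose.

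**Conclusion.** The concern holds as a should-fix. As written, a participant whose operation is abandoned after a block event is dropped from the final comparison of block complications, SAEs and mortality. The allocated technique can cause that exclusion, in an open-label trial where exposure before incision is not the same in both arms.

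The size cannot be derived from the article, because no rate of abandoned operations is given; it is probably small. In the assumed example, even ten such participants in one arm and none in the other leave the SAE test non-significant either way. What is hidden is the direction and size of the excess, not a significant result.

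It would go too far to infer that the main result is at risk. The primary outcome needs a thoracotomy, so the exclusion is defensible there and would stay in place.

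The conclusion assumes that the general population rule governs the safety analyses, which is the plain reading of the text.

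**What to change.** Change the population wording in Statistical methods {20a}, and in the SAP if it follows the same rule:

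1. Limit the no-surgery exclusion to pain, questionnaire and other outcomes that need a thoracotomy.
2. Analyse complications of regional analgesia and SAEs by randomised group in all participants in whom a block was attempted. Using all randomised participants for block complications would add people who never had a block and dilute both rates.
3. Analyse deaths in all randomised participants.
4. Report no-surgery participants with reasons by arm, separating those cancelled before any block from those cancelled after one. This also shows whether cancellation before a block differed by arm, which the block-attempted set cannot show by itself.
5. As a minor tidy-up, describe the comparison groups as those randomised to each technique rather than treated with it.

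The cost is wording and one additional table. Complications, SAEs and deaths are already collected from day 0, and no clinical rule changes. The change should be made before outcome data are compared by arm, because a safety population chosen afterwards in an open-label trial would be hard to defend.

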#### Primary outcome assessment

The primary outcome is the presence of CPTP at 6 months post-randomisation. A mixed effects log-binomial regression model will be used to calculate adjusted relative risks and 95% confidence intervals, adjusting for the intervention group and the minimisation variables. All minimisation variables will be treated as fixed effects, apart from the centre, which will be included as a random effect. The *p*-value from the associated chi-squared test will be produced and used to determine the statistical significance of the estimated treatment group parameter.

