### Sample size {14}

Assuming a 30% incidence of CPTP in the TEB group (similar to that seen in our previous TOPIC-pilot trial results [12] and systematic review [13], 392 patients in each group will give 90% power (two-sided, *p* = 0.05) to detect a 10% absolute reduction (i.e. down to 20%, a 33% relative reduction) in the PVB group. Assuming a 10% rate of death by 6-month follow-up (similar to that seen in the TOPIC pilot) and a further 15% loss to follow-up at 6 months, we will recruit a total of 1026 participants.

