## Assignment of interventions: allocation

### Sequence generation {16a}

Participants will be randomised in a 1:1 ratio to either TEB or PVB. A minimisation algorithm will be used within the online randomisation system to ensure balance in the treatment allocation over the following variables:GenderAge < 65 years or ≥ 65 yearsCentreThoracotomy for lung cancer resection or for other indication

A ‘random element’ will be included in the minimisation algorithm, so that each participant has a probability (1:5), of being randomised to the opposite treatment that they would have otherwise received.

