## Data collection and management

### Plans for assessment and collection of outcomes {18a}

Case report forms will be completed for each individual subject according to Table 3.

**Table 3 Tab3:** Case report forms and data collection

Form name	Contents
Baseline Medical Data Form	Height, weight, ECOG status, ASA grade, performance status, medical history, smoking status and history, lung function,
Patient Completed Booklet Hospital Baseline	Pain questionnaires: VAS, BPI and SF-MPQ-2. QoL – EQ-5D-5L, HADS,
Intervention Form	Analgesia administered in theatre and recovery, intraoperative monitoring, analgesic intervention performed, difficulties and complications with block, local anaesthetic administered
Operation Details Form	Operation type, operator, side, approach, muscle/nerve sparing, rib resection or fractures, chest drainage, histology
Acute Phase patient completed booklet (Day 1^A^, Day 2^A^, Day 3^A^)	Pain questionnaires: VAS and BPI
Acute Day 0^A^ Post Recovery Form	Management of LA block—top-ups, resiting and discontinuation. Analgesia administered. Return to theatre
Acute Phase Up To Day 3^A^ Form	Ward location. Management of LA block—top-ups, resiting and discontinuation. Analgesia administered. Complications and severity (Table 3), return to theatre
Acute Phase Day 4 to Discharge Form	Postoperative analgesia administered. Complications and severity (Table 3), return to theatre
Patient Completed Booklet Hospital Discharge	Patient satisfaction questionnaire. Pain questionnaires: VAS, BPI and SF-MPQ-2. QoL – EQ-5D-5L. HADS
Chronic Phase patient completed booklet (3, 6 and 12 months)	Patient satisfaction questionnaire. Pain questionnaires: VAS, BPI and SF-MPQ-2. QoL – EQ-5D-5L. HADS
Health Contacts Form (3, 6 and 12 months)	NHS Care visits: A&E visits, hospital admissions and investigations received Private healthcare costs. Medications and equipment. Occupation and activities

*ASA grade* American Society of Anaesthetists, *BPI* Brief pain inventory, *ECOG* Eastern Cooperative Oncology Group, *HADS* Hospital Anxiety and Depression Scale, *QoL* Quality of life, *SF-MPQ-2* Short form McGill pain questionnaire, *VAS* Visual analogue score

^A^Day 0 is defined as the day of the intervention (and surgery), Day 1 is first full calendar day (from 12 midnight) post-surgery, day 2 is second full calendar day, day 3 is third full calendar day

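### The primary model omits baseline pain VAS, which is scheduled for all participants and already used for the continuous scores; adding it would gain a little precision at almost no cost

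*Protocol article*

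**What the plan says.** **Primary model.** Under Primary outcome assessment, CPTP at 6 months is analysed with a mixed effects log-binomial model, "adjusting for the intervention group and the minimisation variables". Sequence generation {16a} lists the minimisation variables as gender, age below or from 65 years, centre, and lung cancer resection or another indication. Pain is not among them.

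**Secondary models.** Under Secondary outcome assessment, the questionnaire scores, VAS included, are analysed "adjusting for the intervention group, baseline score (if available) and the minimisation variables". CPTP at 3 and 12 months follows the primary model, so it too carries no baseline term.

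**Baseline data.** Table 2 marks the VAS at the baseline visit. Table 3 lists for the baseline patient booklet "Pain questionnaires: VAS, BPI and SF-MPQ-2. QoL".

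**Sample size.** Sample size {14} states "Assuming a 30% incidence of CPTP in the TEB group" and "392 patients in each group will give 90% power" to detect a "10% absolute reduction (i.e. down to 20%, a 33% relative reduction) in the PVB group". No covariate adjustment is mentioned there.

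**The concern.** The primary outcome is a VAS reading cut at 40 mm, which already discards information. Of the measurements taken before surgery, a VAS pain score is the most direct candidate for explaining part of the remaining variation. The protocol adjusts for it when the 6-month VAS is kept continuous and leaves it out when the same VAS is dichotomised for the analysis that decides the trial. It gives no reason for the difference. Both covariate sets are stated explicitly, so this is a choice made in the text and not a detail left to the analysis plan.

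At stake is the width of the confidence interval for the primary relative risk. Pain is balanced neither by minimisation nor by the model, so chance differences in pre-operative pain between arms remain in the estimate as avoidable noise.

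**Working it through.** **Step 1: reproduce the plan's figure.** The inputs are 30% versus 20% and 90% power (Sample size {14}), "A two-sided *p*-value of < 0.05 will be considered statistically significant" (Statistical methods {20a}), and "Participants will be randomised in a 1:1 ratio to either TEB or PVB" (Sequence generation {16a}). With pooled variance under the null and no continuity correction:

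n = [1.96·√(2·0.25·0.75) + 1.2816·√(0.30·0.70 + 0.20·0.80)]² / 0.10² = (1.2002 + 0.7796)² / 0.01 ≈ 392 per group.

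Inflating in sequence for 10% deaths and a further 15% loss gives 392/(0.90 × 0.85) = 512.4, so 513 per group and 1026 in total. Both stated figures reproduce exactly with no covariate, so the planned 90% does not depend on baseline VAS.

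**Step 2: what baseline VAS could add.** The documents give neither the correlation of baseline with 6-month VAS nor the distribution of baseline pain. Both are assumed here. The model is a normally distributed latent 6-month pain score, cut to give 30% and 20% risk, with correlation r to baseline. R² is the share of the within-arm variance of the binary outcome explained by baseline, averaged over 1500 simulated trials of 392 per group. Adjustment then acts like an effective 392/(1 − R²) per group, and

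power = Φ{[0.10·√(392/(1 − R²)) − 1.96·√0.375] / √0.37}.

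Example, r = 0.3: R² = 0.049, effective n = 412.2, and Φ[(2.0303 − 1.2002)/0.6083] = Φ(1.365) = 91.4%.

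| Assumed r | R² | Power at 392 per group | n per group for 90% |
|---|---|---|---|
| 0 | about 0 | 90.0% | 392 |
| 0.1 | 0.007 | 90.2% | 390 |
| 0.2 | 0.023 | 90.6% | 384 |
| 0.3 | 0.049 | 91.4% | 373 |
| 0.4 | 0.086 | 92.4% | 359 |
| 0.5 | 0.133 | 93.6% | 340 |

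**Step 3: many zero baseline scores.** If 70% of participants score zero before surgery (again an assumption), R² falls to 0.015, 0.034, 0.063 and 0.105 for r = 0.2, 0.3, 0.4 and 0.5. Power is then 90.4%, 91.0%, 91.8% and 92.9%.

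**Step 4: check by simulation.** The same simulated trials were analysed by modified Poisson regression with robust errors, without and with baseline. With no floor, the variance of the log relative risk with baseline was 0.95, 0.95 and 0.87 of that without, for r = 0.3, 0.4 and 0.5. Rejection rates rose from 90.6% to 91.3%, from 89.9% to 91.4% and from 91.1% to 93.9%. The Monte Carlo standard error of each rate is about √(0.9 × 0.1/1500) = 0.8 points, so these support the direction and rough size only.

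**The case against.** The case for leaving the model alone is substantial, and much of it stands.

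- **Nothing is wrong or contradicted.** Adjusting for the minimisation variables is a valid, pre-specified analysis. Randomisation makes baseline pain equal in expectation, and the test's error rate already allows for chance imbalance. This stands in full.
- **The gain rests on an undocumented correlation.** It is small for weak to moderate values and shrinks with a floor at zero. The R² values are also for baseline VAS alone, so any overlap with indication, age or gender would reduce the increment. This stands, and it limits the size of the point.
- **Completeness is not assured.** Tables 2 and 3 show that the VAS is scheduled, not that everyone completes it, and the secondary models use the baseline score only where available. Table 1 names a last-week item for the chronic phase and a last-24-hours item for the acute phase, but none for baseline. Whether the baseline item matches the primary outcome item is therefore not stated.
- **Baseline-adjusted evidence exists elsewhere.** The continuous 6-month VAS analysis and the repeated-measures model both use baseline, and a separate analysis plan, not shown, may hold a supportive analysis. That helps interpretation but does not sharpen the primary estimate.
- **A continuous covariate makes non-convergence of a mixed log-binomial model more likely.** True, but a fallback named in advance deals with it.

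A reader might infer that patients with chest pain of 40 mm or more before surgery distort the comparison because they can count as cases whatever the block does. That concerns the endpoint definition. Such a patient remains a case after a covariate is added, and randomisation makes such patients equally likely in either arm.

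**Conclusion.** The primary analysis omits a baseline measurement that is already scheduled and already used for the continuous version of the same outcome, and so gives up some precision. For assumed correlations of 0.1 to 0.4 the loss is about 0.2 to 2.4 power points at 392 per group. At 0.5 it is 3.6 points. It is less if many baseline scores are zero and nil at zero correlation. These figures rest on a latent-normal model and on correlations that the documents do not supply.

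Two stronger readings are not supported. The omission does not bias the treatment comparison, and the trial is not underpowered because of it, since the stated sample size reproduces without baseline adjustment. Nor do the different adjustment sets contradict one another; they are an unexplained difference. The point is worth acting on because the change costs so little.

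**What to change.** Before database lock, and without sight of outcomes by arm:

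- Add baseline worst chest pain VAS as a continuous covariate (0 to 100) to the primary model and to the CPTP models at 3 and 12 months. State which item and recall period the baseline booklet uses.
- Impute missing baseline values simply, for example with the overall mean ignoring arm, so that no participant with an outcome is dropped.
- Name a fallback in case the mixed log-binomial model does not converge: modified Poisson regression with robust errors, or logistic regression standardised to a relative risk and a risk difference.

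If the sponsor prefers to keep the present primary model, the baseline-adjusted version could be a named sensitivity analysis, with a sentence explaining why the adjustment sets differ.

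The cost is one covariate, one imputation rule and one fallback rule in the analysis plan, and no new data. The downside is a somewhat higher chance that the log-binomial model fails to converge and the fallback has to be used.
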